## Abstract

**Background:**

In Germany, the guardianship system provides adults who are no longer able to handle their own affairs a court-appointed legal representative, for support without restriction of legal capacity. Although these representatives only rarely are qualified in healthcare, they nevertheless play decisive roles in the decision-making processes for people with dementia. Previously, we developed an education program (PRODECIDE) to address this shortcoming and tested it for feasibility. Typical, autonomy-restricting decisions in the care of people with dementia—namely, using percutaneous endoscopic gastrostomy (PEG) or physical restrains (PR), or the prescription of antipsychotic drugs (AP)—were the subject areas trained. The training course aims to enhance the competency of legal representatives in informed decision-making. In this study, we will evaluate the efficacy of the PRODECIDE education program.

**Methods:**

A randomized controlled trial with a six-month follow-up will be conducted to compare the PRODECIDE education program with standard care, enrolling legal representatives (*N* = 216). The education program lasts 10 h and comprises four modules: A, decision-making processes and methods; and B, C and D, evidence-based knowledge about PEG, PR and AP, respectively.

The primary outcome measure is *knowledge*, which is operationalized as the understanding of decision-making processes in healthcare affairs and in setting realistic expectations about benefits and harms of PEG, PR and AP in people with dementia. Secondary outcomes are sufficient and sustainable knowledge and percentage of persons concerned affected by PEG, FEM or AP. A qualitative process evaluation will be performed. Additionally, to support implementation, a concept for translating the educational contents into e-learning modules will be developed.

**Discussion:**

The study results will show whether the efficacy of the education program could justify its implementation into the regular training curricula for legal representatives. Additionally, it will determine whether an e-learning course provides a valuable backup or even alternative learning strategy.

**Trial registration:**

TRN: ISRCTN17960111, Date: 01/06/2017.

## Background

Guardianship is a legal process that transfers decision-making authority over an individual deemed incapable of managing his or her personal and/or financial affairs to another person. Guardianship systems vary widely worldwide by jurisdiction and implementation. In contrast to systems that deny or restrict the legal capacity of a person, the so-called support system allows the person’s legal capacity to remain intact while offering the person support from trusted individuals to make choices [1].

The German guardianship system provides a supportive instrument for the legal protection of adults, without incapacitation or restriction of legal capacity [2]. If an adult is no longer able to handle his or her own affairs due to mental illness or physical and/or mental disability, a legal representative is appointed by court for certain groups of tasks, such as healthcare affairs, that are tailored to the needs of the adult [2, 3]. Approximately 1.3 million people in Germany have been appointed a legal representative [4], of whom 60% are volunteers (family members and others) and 40%, professional representatives [5]. In 65% of the cases, legal representatives are appointed for healthcare affairs [6], with about 20% of professionals due to dementia [5]. Although the legal representatives only rarely have a qualification in the field of healthcare [5], they are nevertheless required to take a major role in decision-making processes for people with dementia [3]. Until now, however, there are no specific authorization criteria and no standardized training courses for legal representatives in Germany [5]. Therefore, core competencies to support healthcare decision-making cannot be presupposed.

Behavioral and psychological symptoms, such as agitation, sleep and appetite changes are common in dementia [7, 8] and may lead to distress in both patients and carers [9]. Interventions such as artificial nutrition via a percutaneous endoscopic gastrostomy (PEG), the use of physical restraints (PR) and antipsychotic drugs (AP) are frequently applied because of anticipated benefits [10–17]. In Germany, the estimated prevalence rates for such interventions on nursing home residents remain high: 5% for PEG [18], 12.5% for PR [18] and almost 30% for AP [17]. There are strong indicators that these autonomy-restricting interventions are more directed towards facilitating nursing care rather than enhancing the quality of life of people with dementia [19]. Evidence for the claimed benefits is weak or controversial, and all interventions have a substantial potential for harm [11, 12, 15, 20–28]. Due to clinical guidelines, interventions are only indicated in exceptional situations [29, 30]. Therefore, it is likely that their use is often not being justified.

The decision-making processes in dementia care are complex and involve different parties, such as physicians, nursing staff, relatives and legal representatives. The attitudes and beliefs of these parties are important factors in explaining these high intervention rates [13, 14]. In order to reduce autonomy-restricting interventions, all parties involved in the decision-making processes should thus be addressed by educational approaches. Several evaluation and implementation studies of educational approaches to reduce PR and AP have been conducted [20, 31–33]. However, legal representatives have not yet been addressed at all.

We developed an education program for legal representatives and tested its feasibility in a pilot study at the University Hamburg, which ran from April 2013 until September 2015 [34]. The aim of the program was to enhance competencies in informed decision processes, as exemplified by the three decisions in the care of people with dementia (PEG, PR and AP). The program was based on the theory of planned behavior and was developed according to the UK Medical Research Council (MRC) evaluation framework as well as methods of evidence-based medicine [35–37]*.* We generated a curriculum based on systematic literature searches and on interviews with voluntary and professional legal representatives and with senior citizens.

In a previous pilot study, we tested the education program for comprehensibility, feasibility, usability and acceptance [34]. We initially conducted eight trainings with 47 legal guardians. The education program was well accepted, and the comprehensibility of contents and materials was rated as high. Participants stated that they developed essential competencies needed to discuss the necessity of PEG, PR and AP in people with dementia, and to aim for alternative interventions. The program appears ready for implementation, but in line with the UK MRC evaluation framework [36], efficacy has to be proven first. To prepare for evaluation in a randomized controlled trial (RCT), we next defined relevant outcome measures and developed appropriate assessment tools. Finally, to pretest the assessment instruments, we carried out the education program five times for a total of 34 legal representatives. Whenever necessary, questionnaires were revised and assessment strategies were optimized.

### Objectives

The main objective of the planned randomized controlled trial is to evaluate the efficacy of the PRODECIDE education program for legal representatives. The key hypothesis is that legal representatives allocated to the education group would achieve a better understanding of decision-making processes and higher levels of realistic expectations regarding probabilities of benefits and harms of PEG, PR and AP to people with dementia compared to the control group.

Understanding the decision-making processes and setting realistic expectations are prerequisites for informed decision-making. Informed and evidence-based decisions may enhance the quality of care of people with dementia and reduce both the overuse and the misuse of autonomy-restricting interventions. Therefore, a further objective is to determine whether the education of legal representatives can result in a clinically relevant reduction of PEG, PR, and AP in persons with dementia.

We expect that implementing the PRODECIDE education program into the regular training offers for legal representatives will be perceived as feasible. To understand barriers and facilitators, a qualitative process evaluation will be performed.

The reporting of this study follows current statements [38, 39].

In parallel to this trial, we will develop a concept for translating the educational contents into e-learning modules, to further support implementation. Web-based learning creates an additional offer that has neither time nor location restrictions. We expect that this alternative could reach people who do not take part in the face-to-face courses. The e-learning modules will be tested for usability. We assume transferability of acceptance and comprehensibility of educational contents.

## Methods/design

### Design

The PRODECIDE-RCT is a randomized controlled superiority trial with two parallel groups, a 1:1 randomization and a six-month follow-up. Together with the trial, qualitative methods will be used to achieve in-depth understanding of the implementation processes. Additional e-learning modules will be developed and tested for usability.

### Setting

The study will mainly take place in northern and eastern Germany in the areas of Hamburg, Schleswig-Holstein, Lower Saxony, Saxony-Anhalt, Berlin and Brandenburg. However, other areas of Germany are not excluded.

Institutions that are established in training professional or voluntary representatives will offer the education program, including regional departments and associations responsible for legal representatives and a leading education institute (*Institut für Innovation und Praxistransfer in der Betreuung* (ipb))*,* organized by the Federal Association of Legal Representatives (*Bundesverband der Berufsbetreuer/innen* (BdB) *e.V.).* The ipb offers training throughout Germany and is intended to support the evaluation.

The education program will be conducted in the University of Hamburg as well as in the cooperating institutions.

### Eligibility and recruitment

The target group for the intervention is legal representatives, both professional and volunteer. Additionally, data will be assessed from all people with dementia who are represented by one of the participating legal representatives at least for 2 weeks within the 6-month follow-up (hereby referred to as *persons concerned*).

Legal representatives who represent at least one person with dementia (assessed by the legal representative and / or medical diagnosis) are eligible for inclusion. Exclusion criteria are former participation in the PRODECIDE education program (either the whole program or a single module).

Recruitment will be performed consecutively in cooperation with institutions that offer training for professional or voluntary representatives. Institution cooperation includes recruitment and conducting the education program. Appointments for the education program will be made, and invitations will be published, using the e-mail lists, websites, calendar of events, flyers, etc., of the cooperating institutions. The invitation covers information about both the education program (e.g., target group, content, place and time) and the study (e.g., randomized allocation, offers for the control group).

Potential participants will register at the study center (by phone, e-mail or fax). After screening for eligibility (by phone), the legal representatives will receive information leaflets, the consent form and forms for baseline assessment (by mail or e-mail).

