Additionally, the number of PEG, PR and AP interventions in the persons concerned will be assessed (Table 1). The legal representatives will perform the assessment as at T0, filling out the documentation sheets and forwarding any copies of routine documentation. New diagnoses since baseline, the presence of PEG, the number and types of PR, medication data and decisions made about one of these interventions will be documented.

All persons concerned who are represented by one of the participating legal representatives at least for 2 weeks within the 6-month follow-up are eligible. If a person concerned who was assessed at T0 is no longer represented by the participant prior to end of follow-up, a documentation sheet will be filled out. The time of and reason for dropout, as well as the presence of PEG, number and types of PR and medication data at the time of dropout, will be documented. New persons concerned during the study period will be assessed at the time of inclusion and at T3. At the time of inclusion, a documentation sheet will be filled out, including time of inclusion, age range, gender, any diagnoses additional to dementia, the presence of PEG, number and types of PR and medication data.

Participants will receive the knowledge test and documentation sheets by mail or, if requested, by email. Participants in the CG have to submit the documents before subsequently beginning the education program (they may hand them over in person on the first training day).

Participants who had not made all three decisions regarding PEG, PR or AP for a person concerned at T2 will be additionally contacted by phone and asked again if they had made a decision since T2. Results of the first decision of each intervention will be recorded as in T2.

To reach a high compliance rate until T3, participants will receive stamped, addressed envelopes for returning outcome assessments by mail. Submission of all documents to the study center will be also possible by email or fax. If required, participants will be reminded by phone, and any of their questions about data assessment will be answered.

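### Eligibility and the persons-concerned outcomes ignore whether the appointment covers healthcare affairs, which can attenuate the secondary PEG/PR/AP results and is not recorded for later checking

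*Protocol article*

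**What the plan says.** All references are to the protocol article.

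- **Background.** Appointment is task-specific: "a legal representative is appointed by court for certain groups of tasks, such as healthcare affairs". On frequency: "In 65% of the cases, legal representatives are appointed for healthcare affairs". That figure covers guardianship cases in general. No share is given for people with dementia.
- **Eligibility and recruitment.** The inclusion rule admits "Legal representatives who represent at least one person with dementia", where dementia may be judged by the participant, by a physician's diagnosis, or both. The only exclusion is earlier exposure to the programme: "Exclusion criteria are former participation in the PRODECIDE education program (either the whole program or a single module". The outcome population is equally broad: "data will be assessed from all people with dementia who are represented by one of the participating legal representatives at least for 2 weeks".
- **Data collection.** The population is restated without a task-area condition: "All persons concerned who are represented by one of the participating legal representatives at least for 2 weeks within the 6-month follow-up are eligible". The T0 items listed for each person are age range, gender, further diagnoses, PEG, restraints and antipsychotics. The sheet for people who join during follow-up has much the same list plus the time of inclusion. Neither list mentions the scope of the appointment, nor do the baseline items on the representatives.
- **Objectives.** Beyond knowledge, "a further objective is to determine whether the education of legal representatives can result in a clinically relevant reduction of PEG, PR, and AP".
- **Data analysis.** The percentages of persons with PEG, restraints (there abbreviated FEM) and AP are calculated per representative at T3 and modelled with the T0 value. Time to the representative's first decision is shown by Kaplan-Meier curves. Those with no decision are censored at six months or at dropout.

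**The concern.** The reduction objective asks whether training the representative changes what happens to the person represented. The main route is the representative's part in the decision, including consent. Where the appointment covers other matters only, that route is closed or much weaker. By the protocol's own account such appointments are common among guardianship cases overall.

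Two consequences follow if the plan is carried out as written. First, persons outside the remit sit in the denominator of the PEG, PR and AP percentages and contribute little or no effect. Second, a representative with no healthcare remit for any person with dementia can enter the first-decision analysis and is likely to be censored. If the trial then found no reduction, readers could not tell an ineffective programme from one given to people without the authority to act on it. Because the remit is not among the listed items, the affected persons could not be picked out afterwards, even for a sensitivity analysis.

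**Working it through.** **1. The plan's own sample size.** Inputs from the Sample size section: difference 0.085, SD 0.17, two-sided 5%, power 90%, dropout 20%. The standardized difference is 0.085/0.17 = 0.5. The two-sample t-test needs 85.03, rounded up to 86 per group, or 172 overall. With dropout, 86/0.80 = 107.5, rounded up to 108 per group, or 216. The plan's figures reproduce. They are based on knowledge at T1, which is measured on the representative and does not depend on any person's remit, so this point leaves them unchanged. The section gives no sample size for the PEG, PR and AP outcomes.

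**2. Attenuation.** Let f be the average share of a representative's persons concerned who are within the healthcare remit, and Δ the true change among them. Assume no change among the rest. The expected change in the percentage outcome is then

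observed change = f × Δ + (1 − f) × 0 = f × Δ.

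The Background section puts AP use in nursing homes at almost 30%. Take a hypothetical fall from 30% to 20% within the remit, so Δ = 10 points. The 65% is the all-cases figure from the Background section. The 80% and 90% are assumptions, used because the share in dementia is not given.

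| f | Observed change |
|---|---|
| 0.65 | 0.65 × 10 = 6.5 points |
| 0.80 | 0.80 × 10 = 8 points |
| 0.90 | 0.90 × 10 = 9 points |

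**3. What restriction would gain.** Let N₀ be the number of in-remit persons needed to detect Δ, and treat persons as the unit with unchanged variance.

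- Without restriction, the effect is fΔ, so N₀/f² persons are needed.
- With restriction, N₀ in-remit persons are needed, which means N₀/f persons among all those represented.
- The ratio is (N₀/f²)/(N₀/f) = 1/f.

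| f | Gain, 1/f |
|---|---|
| 0.65 | 1.54 |
| 0.80 | 1.25 |
| 0.90 | 1.11 |

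The planned model uses one percentage per representative, so these ratios are approximate.

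**4. First-decision analysis.** The analysis follows the representative's first decision. A representative with a mixed caseload has an event as soon as one in-remit decision is made, so out-of-remit persons add no censoring by themselves. Extra censoring comes only from representatives with no healthcare remit for any person with dementia. Their number cannot be derived, because the 65% is a share of cases and not of representatives.

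**The case against.** The case against a large effect is substantial, and most of it stands.

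- The 65% is not specific to dementia. The invitation states the course content, so people with healthcare duties may be more likely to enrol. Randomization also follows receipt of baseline data that include drug names and doses, which a representative without a healthcare remit might be unable to supply. The documents do not describe access rights, so this last filter is inference. The true f may well be above 0.65.
- No effect outside the remit is the extreme case. The Data collection section counts any consideration of an intervention as a decision and allows several parties to initiate it. Informal influence is possible.
- Counting everyone represented is a defensible pragmatic population for a programme meant for regular training.
- The source is a condensed article. The screening form and documentation sheets are not shown and may already ask about task area.

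Three stronger readings are tempting, and the documents do not support them. A reader might infer that the trial needs 1/0.65² = 2.4 times the sample. That compares the diluted analysis with one in which every person is within the remit; restriction also discards persons, so the gain is about 1/f. A reader might infer that every out-of-remit person adds censoring, which step 4 of the working rules out. A reader might infer bias for or against the intervention arm, but randomization balances the remit share in expectation, so the result is attenuation.

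None of this removes the gap. The stated criteria are broader than the objective they serve, and the remit is absent from the stated data items.

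**Conclusion.** The point holds for the secondary outcomes. As written, the eligibility rule and the definition of persons concerned let in appointments that do not cover healthcare affairs, and the listed items do not allow them to be identified. This attenuates the PEG, PR and AP percentages, may add some censored representatives to the first-decision analysis, and weakens the interpretation of a null result.

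The size is uncertain. On the assumption of no effect outside the remit, between one tenth and about one third of the true change would be lost for f from 0.90 down to 0.65 (1 − 0.90 = 0.10; 1 − 0.65 = 0.35). Any informal influence would make the loss smaller. The primary outcome, its analysis and N = 216 stand. The change is worth making because it is cheap and because the remit would be hard to recover later from pseudonymized sheets.

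**What to change.** 1. At the existing telephone screening, ask whether the representative's appointment covers healthcare affairs for at least one person with dementia, and record the answer.
2. Add one box per person (appointment includes healthcare affairs: yes/no) to the T0 documentation sheet and to the inclusion sheet for people who join during follow-up. A box at T0 alone would drop all the newcomers, who have no T0 record.
3. Base the T3 PEG, PR and AP percentages and the first-decision outcomes on persons marked yes at T0 or at inclusion. Report the all-persons result alongside. It keeps the pragmatic reading available and does not depend on a box that, for newcomers, is completed after randomization.
4. Keep all randomized representatives in the knowledge analysis.

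If the sheets already record task area, only steps 3 and 4 need wording.

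The cost is one question, one box and a few sentences. The downside is somewhat fewer persons in the secondary persons-concerned analyses, and possibly some representatives who contribute none. The knowledge outcome loses nothing.

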### Randomization and blinding

After retrieval of written informed consent and baseline data, participants will be allocated to the intervention group or to the control group, stratified by professionals and volunteers (Fig. 1). To ensure a close balance of entities in each group, randomization will be performed by randomly selected block sizes of four and six. The randomization list will be computer generated by a scientist who is not involved in either the intervention or data collection. An independent person will also perform the allocation. As safeguards, no other person will have access to the list, and the list will be sent by e-mail only in an encrypted format.

